### Sample size {14}

Assuming a mean 25-OH-D_3_ = 25 (standard deviation [SD] =12 ) ng/ml based on the data of a recent study [14] with a similar population and vitamin D supplementation to our routine care, 74 infants (37 in each group) affords ≥90% Bayesian power (with a >95% posterior probability) to identify an increase in serum 25-OH-D_3_ in the intervention group, assuming a true increase of 33%. We will assess the largest sample size feasible during the study period of 3 years (≥180 infants) to maximize precision in the estimate of effect and power for other outcomes based on our annual admission rate of infants that will qualify for the study, assuming a consent rate of 60%. Using a neutral Bayesian prior probability (RR = 1.0; 95% CrI, 0.3–3.3), 180 total patients afford 80% power to identify a >80% posterior probability (intervention arm) of reducing respiratory support (based on the described ordinal outcome) assuming a true RR decrease of 20% (RR = 0.80) and 90% power if the true RR decrease is 25%.

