## Statistical methods

### Statistical methods for primary and secondary outcomes {20a}

Intention-to-treat Bayesian analyses [21] will be performed using generalized linear mixed models for all outcomes. Covariates for the primary and secondary outcomes will include the treatment group and BW (<750 g, ≥750 g). All models will also include a random effect for family (to account for within-family correlation). The primary outcome of the 25-OH-D3 level will be analyzed with a linear mixed regression model, and the ordinal respiratory outcome will be analyzed with an ordinal logistic model. Binary outcomes will be analyzed with logistic regression, and data will be counted with a Poisson or negative binomial regression model. Priors will be centered at an odds ratio (RR for count data) of 1.0 (indicative of no difference between treatment groups with a 95% credible interval (CrI) of 0.3–3.3 and in the log OR scale a Normal distribution with a mean of 0 and variance of 0.70). A Normal(0, SD = 10) prior will be used for the intercept term, a Normal(0,1) for all other variables in the model, and half-Normal(0,1) for the SD of the random effect. We will report posterior medians and 95% CrI for group differences, ORs, RRs, and each outcome’s posterior probability of benefit.

All analyses will be conducted in R software latest version. Bayesian models will be fit using Markov chain Monte Carlo (MCMC) methods implemented in Stan via R packages “rstanarm” and “brms.” Each model will be fit using three MCMC chains. Each chain will have at least 5000 burn-in samples and at least 20,000 additional iterations. Convergence of MCMC chains will be assessed by visual comparisons of the trace plots for all parameters from the 3 chains generated for each model. Quantitative checks including the Geweke and Gelman/Rubin tests will be used to ensure convergence to the posterior distribution for all analyses.

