### Methods for additional analyses (e.g., subgroup analyses) {20b}

Subgroup analyses of both RR/odds ratio and risk difference will be performed to assess effect modification by BW, gestational age, sex, race, infants who receive at least 80% of the possible doses (infants with minimal time when feedings were discontinued) and baseline 25-OH-D_3_ level (each assessed in one variable at a time analyses) and of different risk strata (assessed using multiple variables). Bayesian hierarchical models with interaction terms between the treatment group indicator and the prespecified potential modifiers will be used. The conservative Bayesian approach of Dixon and Simon [34] will be applied as it allows for a priori specification of how likely (or unlikely) it is for subgroup differences to be present, and to shrink the subgroup estimates to the overall mean treatment effect. The prior distributions for main effects will be the same for subgroup analyses as for the primary endpoint analysis. A Normal(0, SD = 0.7) will be used for interaction terms. Point estimates of treatment effect and 95% CrI for each subgroup will be reported along with probability of benefit using a forest plot.

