## Discussion

While supplementation with up to 1000 IU/day may be used in many places, we chose 800 IU/day as the intervention arm because it is unlikely to cause toxicity even in EP infants [5]. A fixed rather than a weight-based dose is used because the smaller and more preterm the infant, the higher the risk for vitamin D deficiency, the longer it takes to reach full feedings [14, 35], and the greater the need for growth. Moreover, EP infants may also need a rapid increase in vitamin D levels after birth to optimize intracellular transport [10].

The needs for vitamin D and the metabolism in EP infants may differ from other populations [36, 37]. We will correlate the supplementation regimen, vitamin D metabolite levels analyzed by state-of-art, and clinical outcomes in EP infants. Our findings will help identify levels associated with the best clinical outcomes and avoid assuming that values considered normal in larger and older infants should be the goal values for EP infants [38, 39].

Our measure of respiratory support is ordinal. This avoids using a primary composite outcome (e.g., death or BPD), which gives equal statistical weight to outcomes of differing importance. Moreover, the ordinal outcome allows greater statistical power and a more meaningful assessment [40, 41]. Limitations of traditional frequentist analyses are increasingly recognized, and dichotomous conclusions based on arbitrary *p* value thresholds are increasingly criticized [18, 19]. Bayesian analyses avoid these problems and allow direct assessment of the probability of treatment benefit—what clinicians, patients, and family members want to know—which is not obtainable with standard frequentist analyses [20, 21]. These advantages are particularly important in studies with limited sample size [22]. The posterior probability of benefit will be assessed using conservative neutral prior estimates with a 95% CrI within the range for clinical outcomes almost always found in major randomized trials (RR = 1.0; 95% CrI = 0.33–3.0).

During our trial, we will survey different stakeholders (neonatologists, a random sample of neonatal bedside nurses, and the medical and nursing directors of our NICU) about potential barriers to adopting and implementing higher-dose vitamin D supplementation if our hypotheses are confirmed. This information will position our investigator team to have the largest and quickest impact on patient care after trial completion [42].

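### The treatment-effect prior for OR and RR outcomes is given a variance of 0.70, which does not match its stated 95% CrI of 0.3–3.3 (variance 0.37)

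*Protocol article*

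**What the plan says.** Section {20a} of the protocol article defines the prior for the treatment effect on outcomes analysed as odds ratios, or rate ratios for counts. In one sentence it centres the prior at 1.0 and gives it a "95% credible interval (CrI) of 0.3–3.3 and in the log OR scale a Normal distribution with a mean of 0 and variance of 0.70".

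Three other places bear on this:

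- Sample size {14} bases the power for the ordinal respiratory outcome on a neutral prior with the same interval, but for a relative risk: "Using a neutral Bayesian prior probability (RR = 1.0; 95% CrI, 0.3–3.3". Under it, "180 total patients afford 80% power to identify a >80% posterior probability" of reduced respiratory support.
- The Discussion describes the prior as conservative and neutral and gives a slightly narrower interval: "RR = 1.0; 95% CrI = 0.33–3.0".
- Interim analyses {21b} uses the same statistical approach as the final analysis. It sets two posterior thresholds: above 95% that the risk ratio exceeds 1.15 for death or listed morbidities, and at least 98% for benefit on the ordinal outcome.

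No section says which definition of the prior governs.

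**The concern.** A Normal prior with mean 0 on the log scale is fixed by its SD, so the variance and the 95% interval cannot be chosen separately. If the two halves of the {20a} sentence disagree, a programmer who codes the variance and one who codes the interval fit different models.

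The wider prior shrinks less, so it reaches both the harm and the benefit thresholds on weaker data. That matters most where the data are thin: at the interim, with about 90 of 180 infants, and for rarer morbidities.

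**Working it through.** **1. Reproducing the plan's interval.** The 95% CrI is exp(±1.96 × SD), so the implied SD is [ln(upper) − ln(lower)] / (2 × 1.96).

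| Definition | SD | Variance | 95% CrI |
|---|---|---|---|
| CrI 0.3–3.3 ({14}, {20a}) | (1.194 + 1.204)/3.92 = 0.61 | 0.37 | 0.3–3.3 |
| Variance 0.70 ({20a}) | √0.70 = 0.837 | 0.70 | 0.19–5.15 |
| 0.70 read as an SD | 0.70 | 0.49 | 0.25–3.94 |
| CrI 0.33–3.0 (Discussion) | (1.099 + 1.109)/3.92 = 0.56 | 0.32 | 0.33–3.0 |

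SD 0.61 reproduces the stated interval; variance 0.70 does not. If the limits were rounded to one decimal (0.25–0.35 and 3.25–3.35), the variance could lie between 0.32 and 0.44, still well short of 0.70. Under variance 0.70, the range 0.3–3.3 holds only about 85% of the prior. The 90% interval for SD 0.70 is 0.32–3.16, which does not match either.

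**2. Final power, ordinal outcome.** With estimate SE s, prior variance v and threshold 80%, power = Φ(|ln RR|/s − 0.842 × √(1 + s²/v)). The article gives no category shares, so s was back-solved to 0.131, the value that yields the stated 80% at RR 0.80 under CrI 0.3–3.3. Power at RR 0.80 is then 80.2% (variance 0.70), 80.0% (CrI 0.3–3.3) and 79.9% (CrI 0.33–3.0). At RR 0.75 it is about 91% under all three. If instead 0.80 is read as a proportional odds ratio, with assumed category shares of 15/25/35/10/15% (s = 0.267), the level of power is different, but variance 0.70 and CrI 0.3–3.3 still differ by only 1.4 points. Whether the stated 80% is attainable is a separate question.

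**3. Interim harm rule, single data sets.** With observed log OR b, the posterior mean is m = bv/(v + s²), the posterior SD is √[vs²/(v + s²)], and P(OR > 1.15) = Φ((m − 0.140)/SD). OR stands in for the risk ratio here. The event counts are assumed.

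- 9/45 v 20/45: b = ln 3.2 = 1.163, s = √(1/9 + 1/36 + 1/20 + 1/25) = 0.478.
  - v = 0.70: m = 0.877, SD = 0.415, P = 96.2%.
  - v = 0.37: m = 0.719, SD = 0.376, P = 93.8%.
- 4/45 v 14/45: b = 1.532, s = 0.615. P = 95.8% (v = 0.70) and 92.4% (v = 0.37).

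Both data sets cross 95% only under variance 0.70.

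**4. Interim harm rule, chance of crossing.** Same approximation, 45 per arm. The article gives no death rates, so these are assumptions.

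| True death rate, routine v intervention | Variance 0.37 | Variance 0.70 |
|---|---|---|
| 15% v 15% | <1% | <1% |
| 15% v 20% | 0.4% | 2% |
| 15% v 25% | 3% | 8% |
| 15% v 30% | 10% | 22% |

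For the last row, a fitted logistic model (without birth-weight or family terms) with the rule applied to the risk ratio gives about 15% against 26%. The gap is smaller in relative terms but in the same direction.

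**5. Interim benefit rule.** With the same assumed shares and 90 infants, s = √[12/(90 × 0.934)] = 0.378. The observed OR needed for 98% is 0.43 under variance 0.70 and 0.40 under CrI 0.3–3.3. Data worth 99% under a flat prior give 98.3% and 97.6% respectively, on opposite sides of the bar.

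**The case against.** The strongest reply is that the slip is narrow and the intended prior is easy to identify. The interval 0.3–3.3 appears in both operative sections, the final ordinal analysis hardly depends on the choice, and the interim differences rest on assumed event rates. Most of this stands, and it limits the point:

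- A reader might infer that every decision-driving posterior depends on the conflict. It does not. The prior is stated for odds ratios and rate ratios. The primary 25-OH-D3 outcome uses a linear mixed model, so its >95% criterion is outside the conflict. The biochemical toxicity rule in {21b} uses no posterior probability.
- A reader might apply the 80% bar to rarer binary outcomes. The article sets that bar only for the ordinal respiratory outcome; for the others it promises to report medians, intervals and the probability of benefit.
- A reader might infer that the prior could be picked after seeing data. Nothing in the article suggests this.
- The subgroup section {20b} says "A Normal(0, SD = 0.7) will be used for interaction terms". That is a prior for a different parameter, so it is not a contradiction. It may hint that 0.70 was meant as an SD, but that reading gives 0.25–3.94 and does not rescue the sentence.
- The Discussion's interval differs only slightly (SD 0.56 against 0.61). It could be read as a range seen in other trials, but 0.3–3.3 does not lie within it.

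What the reply does not remove is that one sentence in the analysis section specifies two priors whose variances differ 1.9-fold.

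**Conclusion.** The point holds for OR and RR outcomes. The variance of 0.70 is incompatible with the 95% CrI beside it, and neither rounding nor reading 0.70 as an SD reconciles them. Two smaller mismatches add to it: the Discussion's narrower interval, and the use of the same interval for a relative risk in {14} and for an odds ratio in {20a}, which are not the same prior when outcomes are common.

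The consequence is confined to the posterior-probability rules at the interim and to the posteriors of rarer secondary outcomes. There the choice can move a probability by 2 to 3 points in the worked data sets and roughly double, or more, a small chance of crossing the harm rule. Those sizes rest on assumed event rates, 45 infants per arm and normal approximations. The direction does not depend on the assumed rates: variance 0.70 shrinks less and is less conservative than the prior the article describes.

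**What to change.** State one Normal(0, SD) prior for the treatment effect, name its scale (log OR; log RR for counts), give its matching 95% CrI, and use it in {14}, {20a} and the Discussion and at both the interim and final analyses.

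Because 0.3–3.3 is the interval in both the power and the analysis sections, the natural correction is to replace the variance of 0.70 in {20a} with SD 0.61 (variance 0.37) and to align the Discussion's interval. If the sponsor documents that the wider prior was intended, correct the intervals to 0.19–5.15 instead and re-check the stated power. Either way, {14} should say whether the power calculation put the prior on the RR or the OR scale. If the interim has already been run, record which prior was coded.

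The cost is a short text correction. With SD 0.61 the posteriors are shrunk slightly more than under variance 0.70, so somewhat stronger data are needed to reach the harm and benefit thresholds.

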### Objectives {7}

The objectives are to determine if higher dose supplementation (800 IU/day with any feedings) compared to our routine supplementation regimen (400 IU/day with established feedings) for EP infants during the first 28 days after birth will:Increase the level of 25-OH-D_3_ 1 month after birth by more than 33%Reduce the need for respiratory support at 36 weeks’ PMA with a probability of more 80% (using the ordinal outcome described below and Bayesian analyses)Improve or at least not worsen other secondary outcomes (bronchopulmonary dysplasia; duration of respiratory support; hospital stay; infections; fractures; growth and development through 2 years; and death or individual morbidities)

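### The plan states no priors on the ng/ml scale for the primary linear model of 25-OH-D3; taken literally, its log-scale priors would turn a true 33% increase into a reported 6% to 8% and contradict the stated power at 74 infants

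*Protocol article*

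**What the plan says.** In the protocol article, the section on statistical methods for primary and secondary outcomes {20a} applies generalised linear mixed models to every outcome, with treatment group, birth-weight stratum and a random family effect. For the primary outcome it states: "The primary outcome of the 25-OH-D3 level will be analyzed with a linear mixed regression model".

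It then lists the priors once:

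- **Treatment effect:** centred at an odds ratio (rate ratio for counts) of 1.0, with a 95% interval of 0.3 to 3.3, described on the log scale as Normal with mean 0 and variance 0.70.
- **Intercept:** Normal(0, SD 10).
- **Everything else:** "a Normal(0,1) for all other variables in the model, and half-Normal(0,1) for the SD of the random effect".

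No prior is set apart for the linear model, and no log transformation, standardisation or rescaling is mentioned. Section {20b} carries the main-effect priors of the primary endpoint analysis over to the subgroup models, so the list in {20a} appears meant to cover the primary endpoint.

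The only scale given for the outcome is in Sample size {14}: "Assuming a mean 25-OH-D_3_ = 25 (standard deviation [SD] =12 ) ng/ml". The same section is "assuming a true increase of 33" per cent and claims that "74 infants (37 in each group) affords ≥90% Bayesian power (with a >95% posterior probability" of an increase. Objective 1 is to raise the level "1 month after birth by more than 33" per cent.

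**The concern.** A prior SD near 1 is mild on a log-odds or log-rate scale. In ng/ml, where the outcome SD is 12 and the expected difference is 8.25, it says that the treatment effect almost certainly lies within about 2 ng/ml of zero. The plan's own assumed effect is then more than eight prior SDs out under Normal(0,1), and nearly ten under variance 0.70 (8.25/0.837 = 9.9).

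The other stated priors have the same scale problem. The assumed control mean of 25 lies 2.5 prior SDs from the intercept prior's centre. Half-Normal(0,1) puts 95% of its mass on a family SD below 1.96 ng/ml. Against a total SD of 12, that is a within-family correlation below about 1.96²/144 = 2.7%.

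At stake are the primary effect estimate, the probability attached to the 33% objective, and agreement between the analysis and the sample-size statement.

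**Working it through.** **Inputs.** Control mean 25 and SD 12 ng/ml, true increase 33%, 37 per arm, and at least 180 infants in total, so 90 per arm (Sample size {14}). Allocation is 1:1 (Trial design {8}). Prior variances V = 1 and V = 0.70 come from {20a}. True difference: 0.33 × 25 = 8.25 ng/ml.

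**The plan's own figure first.** Under a flat prior, a posterior probability above 95% matches a one-sided 5% test. Then n = 2 × (1.645 + 1.282)² × 144 / 8.25² = 36.2, so 37 per arm, with power 90.5% (90.0% with the noncentral t). The 74-infant claim reproduces. The two-sided version needs 45 per arm and does not fit.

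**Same calculation with the listed priors in ng/ml.** For a Normal prior with mean 0 and variance V, and known SD:

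- SE² = 2 × 144 / n, which is 7.78 (SE 2.79) at 37 per arm and 3.20 (SE 1.79) at 90
- weight on the data w = V / (V + SE²)
- expected posterior mean = w × 8.25
- power = Φ(8.25/SE − 1.645/√w)

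| Treatment prior (ng/ml) | Per arm | w | Estimate (ng/ml) | % of 25 | Power |
|---|---|---|---|---|---|
| Flat | 37 | 1.000 | 8.25 | 33.0 | 90.5% |
| SD 12 | 37 | 0.949 | 7.83 | 31.3 | 89.8% |
| Normal(0,1) | 37 | 0.114 | 0.94 | 3.8 | 2.8% |
| Variance 0.70 | 37 | 0.083 | 0.68 | 2.7 | 0.3% |
| Flat | 90 | 1.000 | 8.25 | 33.0 | 99.8% |
| SD 12 | 90 | 0.978 | 8.07 | 32.3 | 99.8% |
| Normal(0,1) | 90 | 0.238 | 1.96 | 7.9 | 89% |
| Variance 0.70 | 90 | 0.179 | 1.48 | 5.9 | 77% |

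**Consequence for the 33% objective.** At 90 per arm under Normal(0,1), the posterior SD is √(1 × (1 − 0.238)) = 0.873 and the 95% interval is 1.96 ± 1.96 × 0.873 = 0.25 to 3.68 ng/ml. The true 8.25 lies (8.25 − 1.96)/0.873 = 7.2 posterior SDs above the estimate. For the posterior median to reach 8.25, the observed difference would have to be 8.25/0.238 = 34.7 ng/ml.

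**Check with unknown residual SD.** Gibbs sampling with the Normal(0, SD 10) intercept and a birth-weight term, but no family effect, gave 7.4% to 7.9% (V = 1) and 5.6% to 5.9% (V = 0.70) at 90 per arm, and 3.6% to 4.0% (V = 1) at 37. No draw exceeded 8.25 ng/ml.

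**Sensitivity to scale.** If the outcome is divided by its SD, Normal(0,1) acts like a prior SD of 12 ng/ml and the estimate is 31.3% (37 per arm) or 32.3% (90 per arm). On the log scale, assuming a lognormal outcome with CV 12/25 = 0.48 and hence log SD √ln(1 + 0.48²) = 0.455, Normal(0,1) gives about 32.6% and 32.8%.

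**The case against.** The strongest reply is that the plan never assigns the linear model's treatment term a prior in ng/ml. The treatment prior is written for odds and rate ratios. The Normal(0,1) clause follows the treatment and intercept priors, so it can be read as covering only the birth-weight stratum. On that reading the gap is an unstated Gaussian prior, which an article may leave to its analysis plan. The 74-infant figure also suggests that the authors worked with a vague or rescaled prior.

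Part of this stands. The literal ng/ml reading is an inference from the text, and the shrinkage is not a demonstrated feature of the eventual analysis. But the article goes beyond silence. It names the linear model, fixes numerical priors, and gives ng/ml as the only scale. Even on the milder reading, the intercept, birth-weight and family-SD priors still fall on that scale.

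A reader might also infer several stronger things that the documents do not support:

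- **That power is lost at the planned enrolment.** At 180 infants it is about 89% or 77% for direction. The collapse belongs to the 74-infant claim.
- **That the half-Normal prior causes the 8%.** It does not; the treatment prior alone produces it. How far it understates sibling correlation depends on a correlation that the documents do not give.
- **That every continuous outcome is affected.** Calcium is reported in mg/dl. With an assumed SD of 1 to 2 mg/dl and 90 per arm, w is 0.98 to 0.92 under Normal(0,1) and 0.97 to 0.89 under variance 0.70.
- **That a linear model cannot serve a percentage objective.** A difference can be expressed as a percentage of the control mean.

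**Conclusion.** The concern holds on the literal reading. With Normal(0,1) or variance 0.70 on the treatment coefficient in ng/ml, a true 33% increase would be reported as about 8% or 6% at 180 infants, and the 33% objective would receive essentially no posterior probability. Power at 74 infants would be 2.8% or 0.3% instead of 90% or more. The sample-size statement holds only with an effectively flat or rescaled prior, so sections {14} and {20a} conflict on the ng/ml scale.

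The result rests on the plan's mean, SD and effect, on independent infants, and on the absence of any rescaling. If a log or standardised outcome is intended, the shrinkage nearly vanishes and only the wording is at fault. Because this is the primary analysis, it should be settled before anyone sees unblinded results.

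Other continuous outcomes whose SD is large relative to 1, such as weight in grams or Bayley scores, are exposed in the same way. With an assumed Bayley SD of 15 and 72 per arm (80% of 90), SE² = 6.25 and w = 1/7.25 = 0.138, so a true 5-point effect would be reported as about 0.7.

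**What to change.** Give the linear model priors on its own scale, by one of two routes.

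1. **Log scale.** Analyse log(25-OH-D3) with the existing log-ratio prior and report the ratio of geometric means, which matches the percentage objective. State which prior is meant: the 0.3 to 3.3 interval implies SD ln(3.3)/1.96 = 0.61, while variance 0.70 implies SD 0.84. Either keeps about 99% of the log ratio at 90 per arm.
2. **Original scale.** Standardise the outcome, or multiply the treatment, intercept, covariate and family-SD priors by the outcome SD. A treatment prior SD of at least about 12 ng/ml keeps 95% of the effect at 37 per arm and 98% at 90. The intercept prior should also be centred near a plausible mean.

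If rescaling by the software is intended, say so. Restate the 74-infant power under the prior chosen: about 89.8% with SD 12 ng/ml, or about 85% on the log scale under the lognormal assumption with Normal(0,1). At 180 infants it exceeds 99% either way. Apply the same rule to the other large-scale continuous outcomes.

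The cost is a few sentences in the protocol or analysis plan and a small code change. Enrolment, data collection and sample size are untouched. The log route changes the reported effect measure.
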